**Protocol summary for Supplementation Study**

(Highlight added to indicate sections especially relevant to Vitamin D and growth PlosOne submission)

1. Background

Burden of the TB epidemic: More than 95% of the estimated TB cases and deaths due

to TB occur in developing countries. Mongolia is one of the countries with highest TB

burden in the Western Pacific region. Mongolia is an ideal setting to implement the proposed study given the high prevalence of both TB and vitamin D deficiency, and the government commitment to eradicate TB. Rickets has been a common disease of childhood in Mongolia. Mongols are at high risk for vitamin D deficiency because of their northern latitude, and reduced exposure to UV-B rays during long winter, as well as low availability of vitamin D –rich food (currently no vitamin D fortified food is available in the country). However, the prevalence has even increased over the past 10 years. In 1992, a national nutritional survey by UNICEF with the MOH found that 45% of young children across the country had skeletal abnormalities of rickets. A further survey by World Vision Mongolia and Nutrition Research Center (NRC) of the Public Health Institute found that in 1997 as many as 70% of children less than 5 years of age had one or more of the clinical signs of rickets. The registered incidence of TB had increased from 79 to 141 per 100,000 between 1990 and 2001. Despite the strong effort to control the disease, including nationwide implementation of DOTS, the incidence rate of TB in Mongolia has continued to increase in the last 5 years. It is clear that Mongolians are currently experiencing a heavy burden of vitamin D deficiency. Given the strong scientific rationale for a role of vitamin D deficiency on the incidence and clinical course of TB, and the high prevalence of hypovitamiosis D in Mongolia, the setting is ideal to conduct an intervention study of vitamin D. Although the results would be most directly generalizable to Mongolians, vitamin D deficiency is very common in many populations, including African-Americans, which may also benefit from the findings.

Vitamin D, TB, and Related Infections: Sunshine and cod liver oil both have a long association with the treatment of tuberculosis and represent the two sources of vitamin D available. Earlier report from the mid-19th century suggest that vitamin D in the form of cod liver oil was beneficial in the treatment of tuberculosis. More recent reports have associated low or disturbed serum vitamin D levels with increased susceptibility to tuberculosis and this is supported by genetic linkage studies of vitamin D receptor (VDR) gene polymorphism that indicate an association between the VDR and susceptibility or resistance to tuberculosis. In vitro and animal studies provide evidence of protective relationships between vitamin D and the risks of TB. M. tuberculosis is an intracellular pathogen that resides predominantly within macrophages. There have been many studies on the role of 1,25-D3 on the innate and adaptive immune responses. In general, 1,25-D3 acts to promote the innate immune response to microbial pathogens but to quell what might be an overzealous adaptive immune response to pathogens that prove difficult for the macrophage to handle effectively. Although 1,25-D3 has direct effects on the adaptive immune system, it also affects the ability of the innate immune system to instruct the adaptive immune response. In this instance 1,25-D3 is a potent suppressor of IL-12 production and DC differentiation. Cross-sectional studies indicate that susceptibility to tuberculosis may be increased by deficiency of vitamin D. It was reported that patients with untreated tuberculosis have lower serum level of vitamin D than healthy subjects. Epidemiological evidence suggests a link between vitamin D deficiency and TB. TB is common among Asian immigrants in the UK, and the prevalence of vitamin D deficiency among this population high. A vegetarian diet, which can predispose to vitamin D deficiency, is a strong risk factor for TB in immigrant south London Asians. Despite substantial declines in TB in the United States, blacks continued to have TB at rates eight times greater than whites. Blacks have virtually half the levels of 25(OH)D compared to whites, presumably largely due to lower synthesis in skin with greater melanin content, which blocks UV-B penetration. More epidemiological data support role for innate immunity in human tuberculosis. For instance, in racially integrated nursing homes, infection measured by tuberculin skin test (TST) conversion, occurred twice as often in black as in white individuals who were equally exposed to active TB. In accordance with this, macrophages from Afro-Americans demonstrate a relative permissiveness for intracellular growth of virulent mycobacteria. Intervention studies have examined the role of vitamin D supplements in TB and other infections. In an early intervention study of vitamin D supplements that was carried out in Egypt among tuberculous children TB, clinical improvement was more evident in vitamin D supplemented children (those taking vitamin D) as compared to controls. In another small randomized, double blind intervention study in Indonesia patients were given vitamin D at dose 0.25 mg/day for 6 weeks. One hundred percent of the vitamin D group and only 76.7% of the placebo group had sputum conversion. This difference is statistically significant (p=0.002). There were also more subjects with radiological improvement in the vitamin D group.

The popularity of nutritional supplementation and vitamin D in particular, and the high vitamin D intake from vitamin D fortified food among the patients in developed countries means that the potential extra benefit of supplements might be difficult to detect. These issues can be much more readily studied in developing countries with a high TB prevalence and where background vitamin intakes tend to be low; the results, however, would be generalizable to all persons with low vitamin intakes.

Requirement for Vitamin D: Relative Contributions from Diet and Sunlight Exposure: It is generally accepted that humans evolved from apes in tropical Africa, where full-body sun exposure was a daily occurrence. Dark skin pigmentation, due to melanin, probably evolved in equatorial regions to protect individuals from deadly skin cancers or perhaps other harmful effects of UV-B radiation. Increased skin pigmentation, however, limits the individual’s ability to produce vitamin D3. As populations migrated away from the equator, intensity and duration of sunlight exposure decreased together with skin pigmentation. It was proposed that increased skin pigmentation in humans led to the development of rickets and osteomalacia, pelvic malformations, resulting in an inadequate birth canal with increased maternal and fetal mortality during migration to more northern latitudes. This scenario provided a powerful genetic basis for increased survival of lighter pigmented individuals. Humans cannot achieve adequate amounts of vitamin D from a natural diet since there is essentially no vitamin D in foods that humans normally eat except for fatty fish. In essence, vitamin D, because of its almost total lack in foodstuffs, comes almost exclusively from sunlight, and until very recently in human history, there was no need for oral administration of the vitamin. Previous studies concentrated on how much vitamin D is required to avoid clinical states of deficiency. Available evidence in which circulating intact parathyroid hormone (PTH) and 25(OH)D were measured in adult patients indicates that secondary hyperparathyroidism occurs when serum 25(OH)D values fall below the range of 15-20 ng/mL. This range has become accepted as a critical point for the beginning of vitamin D depletion. Conversely, the range of values for serum 25(OH)D in a sun-rich environment is 54-90 ng/mL.

1. Objectives/Aims/Hypotheses

We propose to examine the following hypothesis and corresponding specific aims:

That improving vitamin D status among healthy children will enhance innate immune response and will protect against TB infection.

A. To recruit subjects, obtain consent, distribute vitamin D supplements to the children in the schools, obtain biologic specimens and to transport those specimens intact back to the United States.

B. To test the hypothesis that daily vitamin D supplementation will increase plasma levels of 25(OH)D, an excellent measure of compliance, and restore TLR-induced antimicrobial activity in monocytes/macrophages tested in vitro.

Overview: We propose a feasibility pilot study with the aim to develop a full prospective study to investigate whether supplementation of vitamin D-deficient individuals with an oral vitamin D can reduce TB infection rate. Specifically, the effect of a daily 800 IU vitamin D supplement will be examined in a randomized trial: Mongolian adolescent children will be randomized to receive a daily vitamin D supplementation and placebo from the start of the study and followed through one school year.

1. Procedure and Intervention

Study design (e.g., double-blind, placebo-controlled, parallel design):

Pilot study to develop the details of the double-blind, placebo-controlled randomized trial of vitamin D in the prevention of TB infection

**Study endpoints:** the primary endpoint for this study is feasibility: 1) recruitment and consent of subjects 2) acquisition of data: height, weight, BMI, survey information (baseline background questionnaire and questionnaire regarding respiratory infection and eczema) and blood 3) compliance with the protocol 4) feasibility of shipping serum samples to the United States without degradation 5) feasibility of cathelicidn induction assay, testing subjects with T-SPOT.TB locally and confirmation of the prevalence of positive skin test at baseline.

Secondary endpoints for this study will be the absolute levels of serum 25(OH)D in the treated and control groups at baseline. Tertiary endpoints include paired differences between serum 25(OH)D at the baseline and end of the pilot study

Primary safety endpoint (study stopping rules): We propose that the DSMB meetings by conference call to decide the “stopping rule” protocol. The treatment is safe, and no case of vitamin D toxicity has ever been documented for vitamin D supplementation below 10,000 IU/day or higher. Based on the Mayo Laboratory Guidelines for 25(OH)D, the upper limit of normal is 80 ng/mL (Mayo Clinics Reference Laboratory, Rochester, MN). Operationally, we will stop vitamin D3 supplementation when if circulating 25(OH)D has exceeded 80 ng/mL serum 25(OH)D; or [2] > 2.75 mmol/L serum calcium. In recently completed studies involving high dose vitamin D3 supplementation resulting in circulating levels of 25(OH)D exceeding 300 nmol (120 ng/mL), there has been no evidence of hypercalciuria, the first indicator of hypervitaminosis D (20) For the purposes of this trial, however, to ensure maximal safety, we have included an upper limit of circulating 25(OH)Dof 80 ng/mL, above which, supplementation will be discontinued.

Study duration: 9 months

Source of Participants: Pupils of the public school # 65 in Ulaanbaatar

Inclusion criteria: Eligible subjects will be children age 12 to 15 years inclusive in public school # 65, located in Songinokhairhan district, who are tuberculin skin test negative, who are residents of Ulaanbaatar, and whose parents have given informed consent and who accent to participate in the study.

Exclusion criteria: Individuals with pre-existing calcium, parathyroid conditions, or type I diabetes, sarcoidosis, or who require chronic diuretic therapy including calcium channel blockers, or who are cognitively impaired, will not be eligible for enrollment into the study. Any individuals with active clinical symptoms of rickets at baseline will not be randomized, but referred to treatment.

Participant recruitment: Once the classrooms are chosen within the schools, a letter will be sent home to parents explaining the study and inviting parents and children to come to one of two or three informational meetings about the study (thus keeping each meeting to 10-20 parent/child pairs) Literacy rates are high in Mongolia (95% of adults can read). [name] will describe the study, answer questions and invite them to participate (perhaps with the participation of [name]). At the completion of the meeting and question and answer period, parents and children will be invited into an adjacent private room, where [name] will administer informed consent and assent procedures, with the school doctor as witness. We will obtain child assent (and parental permission) from all eligible participants ages 12-15.

Early withdrawal of participants: When the participants are withdrawn due to stopping rules or on volunteer basis, their data will be removed from the samples. In case of detection of TB infection, the participants will be referred to the Tuberculosis Surveillance Center, National Center for Communicable Disease for the treatment.

Description: We will use vitamin D produced by Tishcon Corporation, which has produced vitamin tablets for many NIH-funded studies including those conducted by our department among children and pregnant women. Tishcon Corp. [name]

Tiscon is willing to work with us to calibrate the actual IUs to what is said on the label. Like the milk companies, supplement companies produce their products with an overage to ensure the minimum dose in each batch. Tishcon Corp has no direct commercial interest in the results of the project. Tishcon Corp. will have no input in the design, implementation, or outcome of the study.

Treatment regimen: Subjects will be randomly assigned to receive a daily oral dose of one of two treatments from enrollment until the end of the study: (1) vitamin D (800 IU per day), or (2) placebo every school day for total nine months. All the experimental tablets will be identical in color but number-coded. The daily dose of vitamin D (800 IU) that we will use is well under the tolerable upper limit (TUL) of 2000 IU set by the institute of Medicine for children*, and is well below the level of human toxicity. The only known cases of toxicity have involved vitamin D intake greater than 40,000 IU/day. (21). **Standing Committee on the Scientific Evaluation of Dietary Reference Intakes FaNB, Institute of Medicine: Dietary Reference Intakes for Calcium, Phosphorus, Magnesium, Vitamin D, and Fluoride. National Academy Press, Washington, D.C., 1997. Available online at <http://books.nap.edu/openbook.php?record_id=5776&page=285>

Participant compliance monitoring: Substantial consideration has been given to the issue of adherence to the vitamin D intake protocol. First, 14 days after the participant is scheduled to begin taking supplementation they will be called to assess for any symptoms of toxicity. At that time, a series of brief questions will be asked to determine if the participant is having difficulty with adherence, and barriers will be addressed. Any participants who report having difficulty will be contacted again in 3 days to assess adherence and identify any additional strategies that might enhance adherence. Second, at the beginning of each month we will contact all participants and remind them that the next month of supplementation is about to begin, and address any concerns. Finally, children will take the supplementation in the class under teacher’s supervision. We will also collect any remainder pills and count those pills. Finally, we will assess compliance by self-report.

Blinding: Placebo will be provided in tablets, identical in size and appearance to vitamin D tablets. Blinded study medication will be packaged in bottles containing tablets to provide sufficient supply for each month, with overage. All site personnel will be blinded to the treatment arm assignment.

Receiving, storage, dispensing and return: Study subjects will be instructed to return all unused study supplementation in the bottle in which it was dispensed. The study research associate will be responsible for dispensing the study supplementation to participants

Study visits including procedure/tests involved at each visit (e.g., blood test, x-rays, questionnaires)

Treatment randomization will be double blinded.

a) We will recruit 3 classrooms of 100 children, expecting a maximal drop-out/non-completion rate of 10%.

b) Children and parents will complete baseline enrollment forms that query age, gender, economic background, TB contact, medical history for exclusions, and history of BCG vaccination, vitamin and supplementation intake. As part of this proposal, we propose a feasibility study to pilot test the study questionnaires and instruments (i.e., consent forms, self-administered questionnaire on diet, and lifestyle factors) to be used in the subsequent study. Mongolia is one of the countries with the highest tuberculosis burdens in the Western Pacific region. The rapid increase of TB incidence is not only related to improved detection but is also connected with transition hardship and the increase of severe poverty in Mongolia. We believe that the lifestyle factors and nutritional status of the participants assessed by the anthropometric measurements will influence the TB infection rate. In addition to agreeing to take the supplements once a day for the period of nine months, the subjects must consent to undergo a tuberculin skin test (TST) according to national guidelines and provide two 8 ml blood samples.

c) A 8 ml of blood will be drawn and cooled immediately before transportation to the Central Scientific Research Laboratory (CSRL) for further processing for T-cell assay, and where they will aliquotted into 3 x 2 cryotubes, and frozen for vitamin D and cathelicidin assay. White cells will be extracted into a pellet and stored for future genetic analysis, with the collaboration of Mongolian colleagues and if approved by the MOH Ethical Review Board. A fasting blood sample is preferred but will not be an absolute requirement, as the study biomarkers are not appreciably influenced by fasting status.

d) Baseline and endpoint measures will include: height, skin-fold thickness, and weight. The study doctor will also assess clinical signs of rickets and vitamin D deficiency. The study procedures will occur in the local school doctor’s office in private

e) Subjects will be randomly assigned to receive a daily oral dose of one of two treatments from enrollment until the end of the study: (1) vitamin D (800 IU per day), or (2) placebo. All the experimental tablets will be identical in color but number-coded. Vitamin D supplements will be administered as table. We will use vitamin D produced by Tishcon Corporation, which has produced vitamin tablets for many NIH-funded studies including those conducted by our department among children and pregnant women. Tishcon Corp. Placebo is provided in capsules, identical in size and appearance to vitamin D tablets. Blinded study medication will be packed in the ultraviolet (UV) light resistant bottles containing capsules to provide sufficient supply for each month, with overage.

The proposed doses are safe (12, 13) but high enough so as not to miss an effect, if one existed. Clearly, 400 IU vitamin D/day is not enough to sustain adequate nutritional status for many individuals in our society (14). How much oral vitamin D should be administered, particularly in a Mongolian population residing in high northern attitude, to adequately raise the nutritional vitamin D status, is of course, one of the main focuses of our proposed study.

T-cell assay: The current TST is limited because the PPD of tuberculin cannot fully distinguish between infection with TB and history of vaccination with BCG. (According to [name], director of TB Surveillance Center of Mongolia, 30% of Mongolian school children of this age would be tuberculin skin positive). In this study, the ability to diagnose infection with M. tuberculosis in vaccine recipients is critical. In vitro t-cell based interferon release assays use antigens that are encoded by the region of difference (RD-1) so there is no cross-reaction with the BCG vaccine, since these antigens (early secretory antigenic target-6 and culture filtrate protein 10 are absent in the BCG vaccine strains (17).

Antigen-stimulated IFN-gamma production assays are highly suitable for detecting infection; and often-utilized correlate of protective immunity to M. tuberculosis infection (18) and this assay therefore served as a second indicator of the acquired host response. Two assays are currently available as commercial kits: the T-SPOT.TB assay (Oxford Immunotec, Oxford, UK) based on the enzyme-linked immunospot (ELISPOT) principle; and QuantiFERON-TB Gold (QFT-G, Cellestis, Carnegie, Australia). We will use the T-SPOT.TB assay due to its superior ability to detect M. tuberculosis in TB-endemic areas (19). It is approved for sale in Europe, Canada and other countries is being evaluated by FDA for approval. T-cell assay will performed in CSRL under supervision of [name] according to manufacturer directions. Briefly, collected blood is centrifuged, PBMC are collected and resuspended in cell culture medium. Plates are incubated for 16-20 hours after preparing plates by adding cell culture medium, the antigens and control solution. Results will be determined as “reactive” or “non reactive” to TB antigens next day either manually counting the viable cell or using ELISPOT plate reader. The assays are time dependent in that the blood samples need to be transferred to the laboratory within 12 hours.

Randomization procedure:

Follow-up evaluation: There are total four visits during the study: initial, two follow-ups, and final visit (maximum 15 minutes). A background questionnaire on medical and behavioral characteristics of participants will be administered at baseline and repeated 9 months later. At every third month, trained research assistant will visit the school, administer a questionnaire on the health of the study participant in the preceding period, and a school doctors will carry out a complete physical examination. Parameters assessed at visits will include occurrence of symptoms such as fever, cough, and change in appetite and weight. Anthropometric measurements of weight, mid-upper arm circumference, and height will be taken. In addition, the following skin-fold thickness measurements will be done: triceps, biceps, and subscapular.

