The breach of confidentiality is a possible risk. Confidentiality will be maintained by numerically coding data, by disguising identifying information, and by keeping all data in locked file drawers. All information obtained from subjects will be accessible only to research staff. All staff will be trained in confidentiality procedures, and routine refreshers provided.

Safety parameters: The treatment is safe, and no case of vitamin D toxicity has ever been documented for cholecalciferol below 10,000 IU/day or higher. Based on the Mayo Laboratory Guidelines for 25(OH)D, the upper limit of normal is 80 ng/mL (Mayo Clinics Reference Laboratory, Rochester, MN). Operationally, we will stop vitamin D_3_ supplementation when if circulating 25(OH)D has exceeded 80 ng/mL serum 25(OH)D; or [2] > 2.75 mmol/L serum calcium. In recently completed studies involving high dose vitamin D_3_ supplementation resulting in circulating levels of 25(OH)D exceeding 300 nmol (120 ng/mL), there has been no evidence of hypercalciuria, the first indicator of hypervitaminosis D(20) For the purposes of this trial, however, to ensure maximal safety, we have included an upper limit of circulating 25(OH)D of 80 ng/mL, above which, supplementation will be discontinued.

Definition of adverse event and serious adverse event: The major risk of the study is symptoms of hypercalcaemia and hypervitaminosis D. To assess safety among those who are eligible and enroll participants will be informed on potential symptoms of hypercalcemia and asked to call the study coordinator if he or she experiences any such symptoms. Further, we will assess symptoms at the beginning of each month when the next month’s supply of pills is provided, and at week 2 of each month when participants are called to assess problems and adherence. Any symptoms noted will be reported to the study physician, who will make a determination if any reported symptoms are possibly related to vitamin D toxicity. If toxicity due to hypervitaminosis D or hypercalcemia is deemed a possibility, the participant will be asked to discontinue taking the pills and a blood sample for 25(OH)D and calcium will be taken. The local study doctor will determine whether further treatment is necessary.

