**STATISTICAL PLAN AND CHANGES RELEVANT TO NEJM ANALYSIS**

**Analysis Plan for Supplementation Study and Fortification Study Vitamin D and Growth Paper**

*Goal*: to test the extent to which Vitamin D affects physical growth in children (weight, height, and BMI) in Vitamin D versus Placebo or Mongolian +D versus Mongolian regular milk.

1. Check the distribution of the outcome variables

- Run proc univariate and boxplots of each of the following for everyone:
  - Weight at Visit 1
  - Height at Visit 1
  - BMI at Visit 1
  - Weight at Visit 2
  - Height at Visit 2
  - BMI at Visit 2
  - Delta Weight
  - Delta Height
  - Delta BMI
- Repeat for each intervention arm separately
- If things are looking non-normal, try a log transformation and rerun proc univariate and boxplot
- STOP: let’s check degree of missingness in each delta
- STOP: check with [name], [name] and [name] to check normality and decide on any transformation

3. Re-run descriptive statistics from IGF analysis (Fortification Study only) to confirm accuracy for growth variables also evaluating combined 25OHD levels.

- Create table with all information
- (columns by treatment arm)

4. Missingness: for now, let’s do complete case analysis, unless step 2 reveals atrocious missingness, in which case we might want to create missing indicators

5. Then we can start some modeling.

- PROC REG’s for each of the deltas as dependent variables (weight, height, BMI)
  - Create indicator variables for the following interventions: Vitamin D and Placebo for Supplementation Study. Mongolian Regular, Mongolian milk + D for Fortification study. Use the Placebo and Mongolian regular arm as the referent, respectively.
  - Crude model with intervention only
  - Second model adjusted for age, school (Fortification study only), and gender
  - Third model additionally adjusted for compliance [as proportion of intervention received🡪completion
- Also model plasma 25OHD individual change against three growth delta variables (weight, height, BMI)
  - Crude model with 25OHD change only
  - Second model adjusted for intervention arm
  - Second model adjusted for age, school (Fortification study only), and gender and intervention
  - Third model additionally adjusted for compliance [as proportion of intervention received🡪completion

6. Repeat all PROC REG models for the treatment group contrasts with PROC MIXED models

- Crude model with intervention only

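### The Supplementation Study removes withdrawn children's data from the analysed sample, so the arms are no longer as randomised, compliance is probably overstated, and the rate of crossing the safety limits is pushed towards zero

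*Supplement*

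**What the plan says.** **Withdrawal.** Under early withdrawal of participants, the Supplementation Study protocol states: "When the participants are withdrawn due to stopping rules or on volunteer basis, their data will be removed from the samples". It makes no exception for measurements already taken, for compliance records or for safety data. Amendments 1 to 3 leave the sentence as it is.

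**Stopping rule.** The paragraph whose heading begins "Primary safety endpoint (study stopping rules" gives the laboratory limits: "we will stop vitamin D3 supplementation when if circulating 25(OH)D has exceeded 80 ng/mL serum 25(OH)D; or [2] > 2.75 mmol/L serum calcium". The section on safety parameters repeats them.

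**Endpoints.** The primary endpoint is feasibility, and one listed component is "3) compliance with the protocol". The pre-to-post difference in 25(OH)D is a tertiary endpoint.

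**Expected loss.** Under study visits, item a), the plan is "expecting a maximal drop-out/non-completion rate of 10" per cent. Amendment 1 raises enrolment from 100 to 120.

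**Analysis.** The protocol's statistical section compares within-child change between arms by t-test and defines no analysis population. The later plan for the vitamin D and growth paper uses complete cases (step 4), "unless step 2 reveals atrocious missingness, in which case we might want to create missing indicators".

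**The concern.** Withdrawal is a post-randomisation event, and here it can depend on treatment. One trigger is the trial's own 25(OH)D measurement, which vitamin D is meant to raise. Voluntary withdrawal may depend on tolerance, motivation or dislike of the tablets.

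This differs from ordinary missing data because the rule takes out values that were observed. Follow-up visits fall every three months with anthropometry, and Amendment 3 adds mid-winter blood sub-samples. A child who leaves in spring may therefore have post-baseline data, which the sentence discards.

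Three results are exposed:

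- **The comparison between arms**, for 25(OH)D and, in the later plan, for growth.
- **Compliance**, because children who quit have plausibly taken fewer doses than those who stay.
- **The threshold-crossing rate**, because a child stopped for crossing a limit leaves the data in which crossings would be counted.

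The pilot exists to plan a larger trial, so an optimistic compliance figure would carry into that design.

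**Working it through.** **1. The plan's own figure.** The sample-size section gives a minimum detectable difference of 2.63 ng/mL at 80% power. Inputs: pilot SDs 4.8 and 4.5 ng/mL and alpha 0.05 (two-sided assumed), with 100 children split 1:1 (ratio assumed).

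- Pooled SD = √((4.8² + 4.5²)/2) = 4.65.
- Normal approximation: (1.960 + 0.842) × 4.65 × √(2/50) = 2.61.
- Two-sample t-test (noncentral t), 50 per arm: 2.63. The figure reproduces with no allowance for non-completion.

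**2. Loss of precision if 10% are removed** (same SD, t-test):

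| Enrolled | Per arm, all kept | Detectable difference, 80% power | Per arm, 10% removed | Detectable difference, 80% power |
|---|---|---|---|---|
| 100 | 50 | 2.63 | 45 | 2.78 |
| 120 | 60 | 2.40 | 54 | 2.53 |

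At 120 enrolled, power for 2.63 ng/mL falls from 0.87 to 0.83. Power is not the main problem; selection is.

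**3. Compliance.** With a fraction *w* withdrawn after taking a share *q* of doses, and completers taking a share *c*, compliance in all randomised children is (1 − *w*)·*c* + *w*·*q*. The rule reports *c* alone. Assume *c* = 90%:

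| Withdrawn | *q* = 0% | *q* = 50% | Reported |
|---|---|---|---|
| 5% | 0.95 × 90 + 0 = 85.5% | 85.5 + 0.05 × 50 = 88.0% | 90% |
| 10% | 0.90 × 90 + 0 = 81.0% | 81.0 + 0.10 × 50 = 86.0% | 90% |

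The overstatement is 2 to 9 percentage points. The 10% is the plan's maximum for all non-completion, including loss to follow-up, so the 10% row is an upper bound on withdrawals of this kind.

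**4. Threshold crossings.** Suppose 1, 2 or 3 of 60 vitamin D children are stopped for crossing a limit (assumed). The rate is 1/60 = 1.7%, 2/60 = 3.3% or 3/60 = 5.0%. After removal the analysed data show 0/59, 0/58 or 0/57. For 3/60 the exact 95% interval is 1.0% to 13.9%; 0/57 has an upper limit of 6.3%. A crossing first seen at the final blood draw would stay in, since no supplementation is left to stop. Hence 'towards zero' rather than zero.

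**5. How likely is a 25(OH)D stop?** The pilot post-intervention mean was 26.5 ng/mL, SD 4.5. (80 − 26.5)/4.5 = 11.9, so the limit is about 12 SD away (normality assumed). The pilot used fortified milk for one month, so this is a guide only, but such stops should be rare.

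**6. Effect on 25(OH)D.** If completers gain the pilot change, 26.5 − 17.3 = 9.2 ng/mL, relative to placebo, and withdrawn children gain 0–50% of it (both assumed), the all-randomised difference is 9.2 × ((1 − *w*) + *w* × 0 to 0.5). That is 8.7 to 9.0 at 5% withdrawn and 8.3 to 8.7 at 10%.

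**7. Does the later plan repair this?** No. Complete-case analysis does not bring removed children back. The missingness that the plan checks is in the outcome changes in weight, height and BMI. A missing indicator is a device for covariates and cannot supply a missing dependent variable.

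**The case against.** The strongest reply is that the rule does little harm in this trial. Stops for high 25(OH)D are improbable on the pilot figures. There are few blood draws at which the limit could be found crossed, and the visit schedule lists no routine calcium assay. Teachers supervise dosing. This is a feasibility pilot, and the change in 25(OH)D is only tertiary. All of this stands, and it limits the size of the bias. It does not make the rule sound: compliance is part of the primary endpoint, and a safety endpoint must be able to record an event even when none is expected.

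A reader might infer that the rule erases all safety information, so that safety results describe completers only. The documents do not support that. Suspected toxicity leads to a blood sample and physician review, each adverse event generates a case report to both ethics boards, and the monitoring board receives retention, compliance and adverse-event data. The documents do not say whether withdrawn children stay in those summaries or in the reported results.

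A reader might also infer that the rule trims the upper tail of the vitamin D arm alone. That goes too far, since a placebo child can exceed the calcium limit.

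Finally, removal from the samples may mean the analysis sample rather than destruction of records, and for voluntary withdrawal it may reflect consent terms that are not shown. The effect on the analysed results is the same, but the consent terms could limit the remedy.

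**Conclusion.** The sentence is wrong as written and should be changed. Followed literally, it takes collected post-randomisation data out of the analysis, leaves the compared groups other than as randomised, probably biases compliance upward, and makes the analysed threshold-crossing rate uninformative.

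The effect on averages is modest at 10% withdrawn or fewer: about 2 to 9 percentage points of compliance and 0.2 to 0.9 ng/mL on a difference of 9.2, under the assumed intakes and effects. The direction for compliance rests on withdrawn children having taken fewer doses; a child stopped by a laboratory limit may have been fully adherent until then. The threshold-crossing rate is the exception to modest size, because its distortion follows from the rule itself. Voluntary withdrawal is probably the larger source of bias overall.

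**What to change.** Replace the sentence under early withdrawal with wording such as: *Data collected up to withdrawal are kept, unless the family asks for deletion. Children are analysed in the arm to which they were randomised. Already scheduled final measurements are used where the family agrees.*

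Then state in the analysis section:

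- threshold crossings and adverse events are reported in all children who took any tablet;
- compliance is reported in all randomised children;
- withdrawals are tabulated by arm and reason.

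In step 4 of the growth analysis plan, drop the missing-indicator fallback for missing outcome changes. A more elaborate model is not essential: with two visits and only the second missing, children with baseline data alone add almost nothing to the treatment contrast. Obtaining the final measurement matters more.

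None of this alters a dose or a stopping limit. The cost is a few lines of text, some effort to follow withdrawn children to the final visit, and a check of the consent form, which may restrict what can be kept.
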